**1. Trial protocol outline**

(1) Trial food: Food product containing royal jelly (trial project), food product without royal jelly (placebo)

(2) Objective: To evaluate the effects of 8 continuous weeks of consumption of a food product containing royal jelly on subjective assessment of dry eyes as well as ophthalmological examination results, and to compare these effects to those of a placebo.

(3) Subjects: Men and women aged 20 to 60 years with subjective symptoms of dry eyes

(4) Number of subjects at the start of consumption: 50 (trial product: 25 participants; placebo: 25 participants)

(5) Trial design: Randomized, double-blind, placebo-controlled, parallel-group trial

(6) Amount of functional ingredient consumed: Royal jelly 7,200 mg (raw product) per day

(7) Method of consumption: 2 capsules swallowed whole with water after meals, 3 times per day

(8) Period of consumption: 8 weeks

(9) Planned trial duration: May 2014 to March 2015

**2. Trial objective**

The objective is to evaluate the effects of 8 continuous weeks of consumption of a food product containing royal jelly on the subjective assessment of dry eyes as well as ophthalmological examination results, in men and women aged between 20 and 60 years with dry eye symptoms, and to compare these effects to those of a placebo.

4.1. Type and name of trial product

(1) Trial product: Food product containing enzyme-treated royal jelly (RJ)

(2) Placebo: Food product with no RJ

4.2. Consumption history of trial product

This health supplement containing enzyme-treated RJ has been manufactured and sold by Yamada Bee Farm since 2008. As of 2013, more than 1 million bottles had been sold to over 100,000 customers. There have been no reports of serious adverse effects caused by consumption of this product.

4.3. Functional ingredient: RJ

4.4. Composition of trial product

| Per capsule  (approximate value) | | Trial product* | Placebo |
| --- | --- | --- | --- |
| Calories | (kcal) | 2.2 | 2.03 |
| Protein | (g) | 0.16 | 0.15x10-3 |
| Fat | (g) | 0.03 | 0.025 |
| Carbohydrates | (g) | 0.31 | 0.43 |
| Sodium | (mg) | 9.43 | 0.045 |

* Each capsule contains 1,200 mg enzyme-treated RJ (raw product)

4.5. Determination of trial product intake, method of consumption, period of consumption, functional ingredient intake.

(1) Trial product intake, method of consumption.

Two capsules are to be taken unchewed with water after meals, 3 times per day. If subjects forget to take capsules after meals, they can take 6 capsules at one time on that day. Capsules for multiple days should not be taken together. Subjects will record the times and amounts taken in daily journal entries. If they forget to take capsules, this should be recorded in that day’s entry. The subjects should not take any capsules before coming to the clinic on examination days. They can take capsules after the examinations for the fourth week and beyond.

(2) Period of consumption of the trial product.

The period will be 8 weeks (56 days).

(3) Basis for determining functional ingredient intake.

Consumption of 3 to 6 capsules of the RJ product per day was used as a benchmark, with each capsule containing 1,200 g of enzyme-treated RJ (raw product). Clear effects were observed in animal experiments at 300 mg/day, so daily intake for this trial was set at 6 capsules (equivalent to 7,200 mg). Daily intake was also determined based on amounts that were confirmed to be safe in multiple past trials involving other RJ-related products.

**5. Trial design**

Randomized, double-blind, placebo-controlled, parallel-group trial

**6. Number of subjects, allotment method**

6.1. Number of subjects

There will be 50 subjects when consumption is started—25 subjects taking the trial product and 25 subjects taking the placebo.

6.2. Allotment method

The person in charge of allotment will use random numbers to create an allocation table and assign the trial product an allocation number. The person in charge of allotment will then seal the allocation table and keep it sealed until the time comes to open it. After the analysis set and data are fixed, the person in charge of allotment will unseal the allocation table and disclose the information., In the event of a serious adverse event or emergency, the allocation table can be unsealed only to disclose the minimum amount of information required.

7. Inclusion and exclusion criteria for the subjects

People who meet the following inclusion criteria and do not fall under the exclusion criteria will be selected as the subjects.

7.1. Inclusion criteria

(1) Men and women aged between 20 and 60 years.

(2) People who are aware of having dry eyes

7.2. Exclusion criteria

(1) People whose vision when wearing corrective lenses is less than 1.0 in a vision test performed during the preliminary examination

(2) People with severe myopia (-6D or greater)

(3) People who regularly take health foods, supplements, or medical products (including eye drops) that are enriched with the effective ingredient of the trial product (RJ).

(4) People who currently have an ophthalmological disease or have a history of serious ophthalmological disease.

(5) People diagnosed with the following vision disorders: cataracts (congenital, senile, diabetic, concurrent, traumatic), glaucoma (chronic, acute, congenital, secondary).

(6) People who may experience hay fever from July to December or those diagnosed with asthma

(7) People currently undergoing pharmaceutical therapy or people with a history of a critical disease that required pharmaceutical therapy.

(8) People who underwent corrective laser eye surgery in the last 3 months.

(9) People who may have an allergy to the trial product.

(10) People who participated in a clinical trial within 1 month of agreeing to participate in this trial, or who plan to participate in another clinical trial after agreeing to participate in this trial

(11) People who plan to become pregnant or breastfeed during the trial period

(12) People who are otherwise deemed unsuitable by the principal investigator

**8. Subject consent**

8.1. Timing of obtaining consent

Consent should be obtained in writing before the first examination is performed (see examination schedule below).

8.2. Content of explanatory documents

The explanation given to the subjects should cover the following items:

・Name of trial institution, names of principal and other investigators

・Purpose, significance, methods, and duration of this trial (study)

・The voluntary nature of participation in this trial (study)

・The fact that they will not face any disadvantage for not agreeing to participate in this trial (study)

・That they can revoke their consent to participate in this trial (study) at any time

・Any potential benefits, risks, and inevitable discomforts from participating in this trial (study)

・How risks and inevitable discomforts associated with this trial (study) will be compensated for, or otherwise dealt with

・The source of funding for this trial (study), potential conflicts of interest, and relationships the investigators and others have with outside organizations

・How personal and other information will be treated

・That the results of this trial (study) may be published after ensuring the subjects cannot be identified

・Details about joint trials (studies), if any are being conducted

・Where to lodge complaints regarding the handling of personal and or other information

・Things to abide by during the trial (study)

・Delivery of new information, and changes to the trial protocol

・Costs related to the trial (study), and cooperation payments

・How materials will be stored, used, or disposed of after the trial (study) ends, (including that it may be used in other trials, and the expected content of such trials)

・About the ethics committee and publication of summaries of its meetings

8.3. Method of obtaining consent

Following the spirit of the Declaration of Helsinki, subjects will be given the latest explanatory documents and consent forms approved by the ethics committee before taking part in the trial (before the first examination). They will be given a full explanation of the trial and the investigators will strive to answer their questions satisfactorily. The subjects will be given sufficient time to ask questions and decide whether to participate in the trial. The (co-) principal investigator will obtain the consent from the subjects in writing, of their own free will and accord. The consent forms will be dated and signed (or stamped) by the subject and the (co-) principal investigator.

8.4. Delivering information that could affect the subject’s intentions, revisions to explanatory documents and consent form.

If the trial sponsor obtains new and important information that could affect a subject’s consent, it should be quickly communicated in writing to the principal investigator. If the (co-) principal investigator obtains new and important information that could affect a subject’s consent, it should be quickly communicated to the subjects to confirm they are willing to continue the trial. If the principal investigator decides the explanatory documents or consent form need to be revised based on newly obtained information, the revisions should be made quickly, then given to the participants after obtaining approval of the ethics committee to reconfirm their consent (confirm that they are willing to continue the trial).

**9. Protecting personal, and or other information**

The people involved in the trial will give full consideration to protecting a subject’s personal information and privacy when handling the consent forms and case report forms, and when publishing the data. Filling out case report forms, publishing articles, and submitting materials to regulatory authorities should be done in such a manner that a subject cannot be identified (for example assigning them identification numbers) to protect their privacy.

| Examination day | | Preliminary period |  | Consumption period (8 weeks) | | |
| --- | --- | --- | --- | --- | --- | --- |
|  | | Preliminary |  | Pre-consumption | Week 4 of consumption | Week 8 of consumption |
| Inclusion, allotment | |  | ○ |  |  |  |
| Lifestyle questionnaire | | ○ |  |  |  |  |
| Interview | | ○ |  | ○ | ○ | ○ |
| Physical measurements | Height | ○ |  |  |  |  |
|  | Weight | ○ |  | ○ | ○ | ○ |
| Scientific examinations | Systolic blood pressure | ○ |  | ○ | ○ | ○ |
|  | Diastolic blood pressure | ○ |  | ○ | ○ | ○ |
|  | Heart rate | ○ |  | ○ | ○ | ○ |
|  | Biochemical data |  |  | ○ |  | ○ |
|  | Fundoscopy | ○ |  |  |  |  |
|  | Vision test, refractometry | ○ |  |  |  |  |
|  | Functional visual acuityt |  |  | ○ | ○ | ○ |
|  | BUT | ○ |  | ○ | ○ | ○ |
|  | Keratoconjunctival disorder | ○ |  | ○ | ○ | ○ |
|  | Schirmer’s test | ○ |  | ○ | ○ | ○ |
| Subjective dry eye evaluation | DEQS | ○ |  | ○ | ○ | ○ |
| Consumption of trial product | |  |  | [figure not shown] | | |
| Journal records | |  |  | [figure not shown] | | |

**10. Schedule and examination content**

10.1. Trial schedule

(1) Preliminary examinations will be performed on candidate subjects who give consent. These will include a lifestyle questionnaire, interview, physical measurements, scientific measurements, ophthalmological examinations ( fundoscopy, vision test, refractometry, Schirmer’s test), and subjective evaluation of dry eyes (questionnaire).

(2) Fifty people who fit the objective of the trial will be selected based on the results of the preliminary examinations.

(3) The subjects who are selected will come to the clinic for pre-consumption examinations, which will include an interview, physical measurements, scientific measurements, ophthalmological examinations (functional vision test, break-up time of tear film (BUT), keratoconjunctival disorders), and subjective evaluation of dry eyes (questionnaire).

(4) After the pre-consumption examinations, the subjects will be given the allotted trial product so that they can begin taking it the following day. They will also begin making journal entries of details such as the time they consume the trial product.

(5) The subjects will come to the clinic during the fourth and eighth weeks of the trial to undergo physical measurements, scientific measurements, and ophthalmological examinations (functional vision test, BUT, keratoconjunctival disorders, Schirmer’s test).

10.2. Examination days

The subjects will come to the clinic a total of 4 times for examinations. If a subject cannot undergo an examination on the designated day for some reason, the principal or co-principal investigator will decide on another day to perform the examination that is within 7 days before or after the designated day. If necessary, repeat examinations and follow-up examinations will be conducted.

10.3. Survey and examination content

See the schedule above.

| Item | Content | |
| --- | --- | --- |
| Lifestyle questionnaire | Medical history, medical product and health food intake, allergies, smoking status, alcohol intake, subjective dry eye symptoms (DEQS), etc. | |
| Interview | Inquire about physical condition, check for adverse events | |
| Physical measurements | Height*^1^, weight, BMI | |
| Scientific examinations | Systolic blood pressure, diastolic blood pressure, heart rate, biochemical data(total protein, aspartate aminotransferase, alanine transaminase, lactate dehydrogenase, alkaline phosphatase, gamma-glutamyl transferase, urea nitrogen, creatine, uric acid, total cholesterol, low-density lipoprotein cholesterol, high-density lipoprotein cholesterol triglyceride, glucose, haemoglobin A1c) | |
|  | Fundoscopy | Examination by physician during interview*^1^ |
|  | Vision test | Measured using a visual examination device*^1^ |
|  | Functional vision test, | Examined using a functional optometer*^2^ |
|  | Refractometry | Examined using autorefractor keratometer*1 |
|  | BUT | Fluorescein BUT*^2^ |
|  | Keratoconjunctival disorder | Fluorescein stain test*^2^ |
|  | Schirmer’s test | *^3^ |

1. ^1^: Performed at preliminary examination only
2. ^2^: Performed starting with pre-consumption examination
3. ^3^: Performed at preliminary examination and eighth-week examination

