**15. Evaluation methods**

15.1 Evaluating efficacy

(1) Primary outcomes: subjective dry eye symptoms, BUT, keratoconjunctival disorders, Schirmer’s test

(2) Secondary outcomes: functional vision

(3) Efficacy evaluation methods

For each item, values before consumption and at each time point after consumption will be compared between the trial group and the placebo group using a 2-sample t-test. The amount of change from before consumption to each time point after consumption will be compared between the trial group and the placebo group using a 2-sample t-test. Values at each time point after consumption will be compared to values before consumption in each group using a 1-sample t-test.

For the baseline characteristics of patients with dry eye, Student’s t-test (p ≥ 0.05 by the F-test) will be used for comparison of age, and Pearson chi-square test will be used for categorical data of gender and dry eye diagnosis. Repeated measures analysis of variance followed by Tukey's honest significant difference (HSD) post hoc test will be used for analysis of dry eye symptoms. For the biochemical analysis, paired t-tests will be used for within-group comparisons and the F-test, followed by Student’s t-test (p≥0.05 by the F-test) will be used for between-group comparisons (placebo vs. RJ). A p-value of <0.05 was considered statistically significant. 16.2. Evaluating safety

(1) Outcomes

These are adverse events confirmed from interviews and journal entries (subjective symptoms), and abnormal variations in body weight and scientific examination values. For examination values, changes in items will be checked: body weight, systolic blood pressure, diastolic blood pressure, heart rate, and biochemical data.

(2) Evaluation methods

The number of adverse events and abnormal variations will be totaled to create a table. If the same adverse event occurs in the same subject multiple times, it will be treated as one event. To evaluate changes in examination values, measurements before consumption and at each time point after consumption will be compared using a 1-sample t-test. Figures will be displayed as mean ± standard deviation (or standard error). The significance level will be 2-sided 5%.

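### Schirmer's test, one of four primary outcomes, has three incompatible visit schedules, and two of them omit the pre-consumption value that the change analysis needs

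*Protocol*

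**What the plan says.** Section 15.1 lists the "Primary outcomes: subjective dry eye symptoms, BUT, keratoconjunctival disorders, Schirmer’s test". For each item it plans a between-group comparison of values before consumption and at each later time point, a within-group comparison with the value before consumption, and this: "The amount of change from before consumption to each time point after consumption will be compared between the trial group and the placebo group".

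Three places in the protocol say when Schirmer's test is done:

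- **Examination schedule table** (printed just before section 10): the row "Schirmer’s test" is marked at preliminary, pre-consumption, Week 4 and Week 8.
- **Section 10.1:** item (1) includes the test at the preliminary visit. Item (3), for the pre-consumption visit, lists "ophthalmological examinations (functional vision test, break-up time of tear film (BUT), keratoconjunctival disorders), and subjective evaluation of dry eyes (questionnaire" and does not name it. Item (5), for Weeks 4 and 8, lists "ophthalmological examinations (functional vision test, BUT, keratoconjunctival disorders, Schirmer’s test" and does.
- **Section 10.3, footnote 3**, attached to Schirmer's test alone: "Performed at preliminary examination and eighth-week examination".

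Section 10.3 refers the reader back to the table, which its own footnote contradicts. No rule says which source prevails.

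**The concern.** All three statements are current protocol text. The table row is intact, section 10.1 is prose and the footnote is a plain sentence, so damaged table extraction does not explain the conflict.

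Staff who work from section 10.1 would take no Schirmer value at the pre-consumption visit. Staff who work from footnote 3 would take none at Week 4 either. Neither value can be recovered later, and a statistical analysis plan cannot supply it.

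The only untreated Schirmer value would then come from the preliminary visit, and section 10.1(2) selects the 50 subjects on the results of that visit. A before-after change measured from a selection visit can contain regression to the mean.

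There is also a smaller consequence. Section 14.1 limits the efficacy set to subjects who complete the whole designated schedule, and for this outcome that schedule is not uniquely defined.

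**Working it through.** The protocol gives no figure to reproduce here. The check sets the passages side by side and counts the analyses each would support.

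**Step 1. Visits at which Schirmer's test is scheduled**

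| Source | Preliminary | Pre-consumption | Week 4 | Week 8 | Total |
| --- | --- | --- | --- | --- | --- |
| Schedule table | yes | yes | yes | yes | 4 |
| Section 10.1 (1), (3), (5) | yes | no | yes | yes | 3 |
| Section 10.3, footnote 3 | yes | no | no | yes | 2 |

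Only the preliminary and Week 8 values are common to all three.

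**Step 2. Change comparisons available for section 15.1** (Week 4 and Week 8, so two are intended)

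| Baseline used | Table | Section 10.1 | Footnote 3 |
| --- | --- | --- | --- |
| Pre-consumption visit | 2 | 0 | 0 |
| Preliminary visit | 2 | 2 | 1 (Week 8) |

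Section 15.1 says only "The amount of change from before consumption to each time point after consumption". It does not say which visit supplies the value before consumption.

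**Step 3. What the preliminary visit would do as baseline**

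This step needs assumptions that the protocol does not supply. Let the preliminary and later Schirmer values be standard bivariate normal with test-retest correlation r and no treatment effect.

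- *No selection on Schirmer values or a correlate of them:* expected change is 0, and the within-group test keeps its 5% error rate.
- *Illustrative selection of below-median values only:* the selected mean is −√(2/π) = −0.798 SD, so expected change is 0.798 × (1 − r). Its variance is (1 − r)² × (1 − 2/π) + (1 − r²), with 1 − 2/π = 0.363.

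For a 1-sample t-test in one arm of n = 25, the noncentrality is √25 × mean/SD:

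| r | Mean change (SD units) | SD of change | Noncentrality | Two-sided rejection rate |
| --- | --- | --- | --- | --- |
| 0.5 | 0.798 × 0.5 = 0.399 | √(0.25 × 0.363 + 0.75) = 0.917 | 5 × 0.399/0.917 = 2.18 | 55% |
| 0.7 | 0.798 × 0.3 = 0.239 | √(0.09 × 0.363 + 0.51) = 0.737 | 5 × 0.239/0.737 = 1.62 | 34% |
| 0.8 | 0.798 × 0.2 = 0.160 | √(0.04 × 0.363 + 0.36) = 0.612 | 5 × 0.160/0.612 = 1.30 | 24% |

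In the same model, simulated with 25 per arm, the 2-sample t-test of change between arms rejects in about 5% of trials at every r. Both arms come from the same selected pool, so the expected regression cancels.

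**Step 4. The other visit differences**

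- *Questionnaire (DEQS) and interview:* the table marks both at all four visits. Section 10.1(5) names neither at Weeks 4 and 8.
- *BUT and fluorescein staining:* the table marks both at the preliminary visit. Footnote 2 says "Performed starting with pre-consumption examination", and section 10.1(1) does not list them. All versions agree on pre-consumption, Week 4 and Week 8, so no planned change comparison is affected.

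**The case against.** Three objections carry weight.

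First, no version leaves Schirmer's test without any before-after pair. A preliminary and a Week 8 value appear in all three, so it would be wrong to infer that the outcome cannot be analysed. This stands. The loss is limited to the pre-consumption value (section 10.1 and footnote 3) and the Week 4 value (footnote 3 only).

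Second, a reader might take the 24% to 55% above as the trial's false-positive rate. The documents do not support that. Section 7.1 asks only for age 20 to 60 and awareness of dry eyes, section 7.2 has no Schirmer threshold, and section 10.1(2) says only that those who fit the objective are chosen on preliminary results. Below-median selection is an assumption, and the no-selection end of the range gives 5%. The inflation also touches only the within-group test, whereas the objective is the comparison with placebo.

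Third, a reader might infer from section 10.1(5) that no questionnaire is collected after baseline. The table schedules it at Weeks 4 and 8, section 10.3 refers to the table, and section 15.1 plans a repeated-measures analysis of symptoms. No passage says that it is not done. The list in 10.1(5) is incomplete and is not a rival schedule.

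None of this removes the Schirmer conflict. Footnote 3 is a positive statement about which visits include the test, and it disagrees with both other sources.

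**Conclusion.** The point holds for Schirmer's test. One of four primary outcomes has three incompatible schedules, of 4, 3 and 2 measurements. With a pre-consumption baseline, section 10.1 and footnote 3 each leave none of the two intended change comparisons. With the preliminary visit as a substitute baseline, footnote 3 still leaves only Week 8.

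The conclusion rests on the text alone and needs no statistical assumption. The regression-to-the-mean consequence is conditional: it arises only if the preliminary visit serves as baseline and selection depends on Schirmer values or something correlated with them. Its size then runs from none upward, and it would distort the within-group test without biasing the randomized between-group comparison.

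The omissions in section 10.1(5) and the disagreement over BUT and staining at the preliminary visit are drafting faults. Neither removes a planned change analysis if the table is followed.

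**What to change.** Before the first visit:

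1. Reconcile the schedule table, section 10.1 (1), (3) and (5), and footnote 3 of section 10.3 to one schedule. For the analysis in section 15.1, Schirmer's test has to be done at the pre-consumption visit and at every post-consumption visit that is analysed.
2. State in section 15.1 that the value before consumption is the one from the pre-consumption visit, not the preliminary visit.
3. As drafting corrections, add the questionnaire and interview to section 10.1(5) to match the table, and make footnote 2, section 10.1(1) and the table agree on whether BUT and staining are done at the preliminary visit.

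The cost is a text correction and up to two more Schirmer measurements per subject relative to footnote 3 (pre-consumption and Week 4: 4 − 2 = 2), or one relative to section 10.1 (4 − 3 = 1). They fall at visits already held and already marked in the table, so no visit is added.
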